## Abstract

**Background:**

Sleep apnea and coronary artery disease are prevalent and relevant diseases. The mechanism by which sleep apnea leads to coronary artery disease remains unclear. Intermittent hypoxia, caused by sleep apnea, leads to inflammation and consequent endothelial dysfunction. Endothelial dysfunction precedes the development of atherosclerotic disease and the occurrence of cardiovascular events. Agents that potentially act to improve endothelial function can help prevent cardiovascular events. Patients using immunomodulators due to rheumatic diseases have a lower prevalence of cardiovascular diseases. However, the potential cardioprotective effect of these drugs in patients without autoimmune diseases is not clear. Hydroxychloroquine (HCQ) is an immunomodulator used to treat rheumatoid arthritis and systemic lupus erythematosus. In addition to its anti-inflammatory properties, HCQ reduces cholesterol and blood glucose levels and has antithrombotic effects. The drug is inexpensive and widely available. Adverse effects of HCQ are rare and occur more frequently with high doses.

**Objective:**

In this randomized clinical trial, the effect of HCQ treatment on endothelial function will be tested in seniors with sleep apnea.

**Methods:**

We will recruit participants over the age of 65 and with moderate-severe sleep apnea from an ongoing cohort. We chose to use this sample already evaluated for sleep apnea for reasons of convenience, but also because the elderly with sleep apnea are vulnerable to heart disease. Endothelial function will be assessed by examining flow-mediated dilation of the brachial artery, the gold standard method, considered an independent predictor of cardiovascular events in the general population and by peripheral arterial tonometry, the most recent and most easily obtained method. Hydroxychloroquine will be used at a dose of 400 mg/daily for 8 weeks.

**Discussion:**

Our study aims to obtain evidence, albeit preliminary, of the efficacy of hydroxychloroquine in improving endothelial function and reducing cardiovascular risk markers. If the improvement occurs, we plan to design a randomized multicenter clinical trial to confirm the findings.

**Trial registration:**

ClinicalTrials.gov NCT04161339. Registered on November 2019.

## Administrative information

The order of the items has been modified to group similar items (see http://www.equator-network.org/reporting-guidelines/spirit-2013-statement-defining-standard-protocol-items-for-clinical-trials/).

## Introduction

### Background and rationale {6a}

#### Obstructive sleep apnea (OSA) and cardiovascular disease

In a meta-analysis, the prevalence of sleep apnea in the general adult population ranges from 6% to 17%, reaching 49% at advanced ages [1]. In a Brazilian epidemiological study, OSA affected 80 to 95% of the elderly [2]. The most damaging consequence of OSA is an increase in cardiovascular morbidity and mortality [3]. Cardiovascular diseases are responsible for 20% of deaths of Brazilians over 30 years old and lead to increased morbidity and mortality in over 30% of the elderly [4]. Prospective population studies have shown that individuals with severe untreated sleep apnea have a higher risk of general and cardiovascular mortality, independent of traditional cardiovascular risk factors [5]. Apnea patients, compared to the general population, are twice as likely to have hypertension [6], ischemic heart disease [7], and cerebrovascular disease [8]. In 2004, the National Heart, Lung, and Blood Institute committee proposed lines of research to enlighten the consequences of sleep disorders in heart disease [9]. In 2008, the American Heart Association and the American College of Cardiology published a consensus indicating the need for researches like ours that addresses the major cardiovascular consequences of sleep apnea [10]. The main reasons why sleep apnea is associated with cardiovascular diseases are the periods of intermittent hypoxia and the repeated nocturnal awakenings precipitated by apneas. Apnea occurs when anatomical and/or functional changes in the airway, associated with loss of tone in the pharyngeal dilator muscles during sleep, lead to airway collapse and interruption of airflow. Nighttime awakenings cause chronic sympathetic hyperactivity and intermittent hypoxia causes oxidative stress, which causes inflammation, the onset of endothelial dysfunction and, later, atherosclerosis. The association between coronary artery disease and sleep apnea appears to be consistent. In a cross-sectional analysis of the Sleep Heart Health Study cohort, individuals in the highest quartile of apnea-hypopnea index present a 27% risk increase for coronary artery disease. Sleep apnea increases the chance of having ischemic heart disease by 65% [11] and having a heart attack by 71% [12]. Our group demonstrated that sleep apnea is a more robust risk factor for coronary artery disease than classic factors such as cholesterol, in a sample excluding morbidly obese, diabetic, and smokers [13].

#### Endothelial function

The endothelium, by isolated area, is one of the largest organs in the body, composed of trillions of cells, weighing more than 1 kg and covering almost 3 m^2^ in a 70-kg adult male [14]. It interacts with multiple systems and has been implicated in the pathogenesis of neurological, renal, liver, vascular, dermatological, immunological, and cardiovascular diseases. It is a highly specialized tissue, responsible for vascular homeostasis through the regulation of arteriolar tone, platelet aggregation, smooth muscle cell growth, and leukocyte adhesion. The endothelium regulates the vascular tone through the secretion vasodilator, such as nitric oxide (NO), and vasoconstrictors, such as endothelin. Damage to the endothelium and dysfunction of this tissue are associated with the development of arterial hypertension and atherosclerosis. There are many molecular and cellular mechanisms involved with endothelial damage and vascular aging. Since inflammation and oxidative stress are part of these mechanisms, tackling these two processes can be considered as future therapeutic targets for the prevention of cardiovascular disease [15]. A review article on the topic states that a greater understanding of endothelial function provides not only a grasp of the pathophysiology of cardiovascular disease but also an opportunity for clinical treatment, early detection of diseases, stratification of cardiovascular risk, and evaluation of therapeutic response [16].

#### Flow-mediated dilatation of the brachial artery

The assessment of flow-mediated dilation (FMD) was first introduced in the 1990s as a non-invasive approach to examining vasodilator function in vivo. The FMD result quantifies the endothelium-dependent arterial function mediated by nitric oxide, being used as an indirect marker of vascular health [17]. A meta-analysis that included 32 studies and 15,000 individuals concluded that the FMD result is an independent predictor of cardiovascular events and death. Each 1% dilation increase in the FMD result was associated with a 10% lower risk of cardiovascular event or death. In that study, the predictive effect of brachial FMD was more substantial for cardiovascular mortality than for general mortality, suggesting that impaired endothelial function is predominantly a cardiovascular risk factor [18].

The method has limitations that must be considered. Small changes in the methodological approach can critically influence results and decrease exam reproducibility. Therefore, the compliance of guidelines with updated and standardized methodology is indicated to reduce measurement errors and improve FMD reliability in clinical studies [19].

#### Peripheral arterial tonometry

Peripheral arterial tonometry (PAT) is a non-invasive method of assessing endothelial function in clinical practice. The method was incorporated into several population and multicenter studies, such as the Framingham Heart Study. The results are based on digital pulse amplitude variation during reactive hyperemia induced by a 5-min forearm cuff occlusion. It is operator/interpreter independent and provides immediate results, which are advantages compared to FMD. The reactive hyperemia index (RHI) obtained by PAT is considered to correlate significantly with coronary endothelial function [20]. PAT is a predictor of cardiovascular risk in high-risk patients, according to several authors [21–24]. The method also has good reproducibility, according to studies by Brant et al and Reisner et al. [25] In two large population studies, totaling more than 10,000 participants, there is only a modest correlation between FMD and PAT [26, 27]. Therefore, both methods will be used in this study, in order to quantify aspects of both macro- and microvascular circulation and compare the two methods.

#### Endothelial function and obstructive sleep apnea

Sleep apnea is related to systemic inflammation, oxidative stress, and endothelial dysfunction [28, 29]. These factors are protagonists in the process that leads patients with sleep apnea to develop cardiovascular disease. The association between endothelial dysfunction and sleep apnea was initially considered ambiguous because there are numerous common features among patients with endothelial dysfunction and sleep apnea. Age, obesity, smoking, and alcohol consumption were factors cited as potential causes of the two conditions, confusing a possible cause-effect relationship. A meta-analysis by Wang et al. concluded that moderate/severe sleep apnea was significantly associated with endothelial dysfunction, increased arterial stiffness and increased serum levels of inflammatory markers. The meta-regression data suggest that the adverse effect of moderate-severe sleep apnea on endothelial function is not modified by potential confounders, such as body mass index [30]. Cross-sectional analyses of population studies and case-control studies consistently demonstrated an association between obstructive sleep apnea and impaired endothelium-dependent vasodilation [31]. In vitro experiments demonstrate that the serum of patients with sleep apnea impairs the migration of coronary endothelial cells [32]. Our group published studies demonstrating that intermittent hypoxia causes oxidative stress [33], inflammation, and damage to lipids and proteins [34].

#### Hydroxychloroquine

Hydroxychloroquine was initially an antimalarial drug. Due to its anti-inflammatory properties, it is commonly used to treat rheumatic diseases, in particular rheumatoid arthritis and connective tissue diseases such as systemic lupus erythematous. HCQ reduces the activation of the innate immunity system by inhibiting the stimulation of Toll-like receptors [35], which can play an important role in the activation of inflammatory cells in atherosclerotic patients [36]. Some studies suggest that hydroxychloroquine also reduces the production of cytokines important in the pathogenesis of atherosclerosis, such as interleukin-1 and 6 and tumor necrosis factor alpha (TNF-α) [37, 38]. TNF-α block therapy was associated to a risk reduction of coronary artery disease among patients with rheumatoid arthritis [39].

In addition to its anti-inflammatory effects, HCQ has other properties that may be beneficial in the treatment of coronary artery disease [40]. In patients with lupus, chloroquine inhibits the synthesis of several members of the matrix metalloproteinase family, especially MMP-9 [41], enzymes capable of degrading interstitial collagen in the fibrotic layer of the atherosclerotic plaque [42].

Cohort studies have shown that HCQ lowers cholesterol in patients with lupus and rheumatoid arthritis [43–46]. In addition, in rheumatoid arthritis, the use of HCQ has been associated with a lower incidence of type 2 diabetes [47–49], lower levels of glycosylated hemoglobin (HbA1c) [50], and better sensitivity to insulin and beta cell function [51]. In two randomized studies of diabetics with inadequate glycemic control, HCQ significantly reduced glucose levels [52, 53].

In addition, HCQ may have antithrombotic properties [54, 55]. In mice, HCQ reduced the size and duration of the thrombus and caused a decrease in the thickness of the vascular wall and the progression of atherosclerosis [56, 57]. In a case-control study, among patients with lupus, the use of HCQ was associated with a reduced risk of thromboembolic complications [58].

Sharma et al. reported in a retrospective study involving 1266 patients with rheumatoid arthritis an association between HCQ use and a 72% reduced risk of an outcome composed of acute coronary syndrome, cardiac revascularization, stroke, transient ischemic accident, peripheral arterial disease, and sudden death [59].

Evidence from studies in patients with rheumatic diseases converges to a role for HCQ in reducing cardiovascular risk. However, its cardiovascular effects in patients at higher cardiovascular risk but without rheumatic diseases are unknown.

Some common side effects of hydroxychloroquine, occurring in 1-10% of users, include anorexia, emotional lability, headache, blurred vision, abdominal pain, nausea, rash, and itching. Rarely, in 0.1–1% of high-dose users, Stevens-Johnson syndrome, cardiomyopathy, and retinopathy may occur.

#### Overall

Considering that sleep apnea is a chronic disease with an inflammatory component, as well as rheumatic conditions, HCQ, due to its favorable effects in the reduction of several cardiovascular risk factors, may improve endothelial dysfunction associated with sleep apnea.

Considering the low cost of HCQ, the high prevalence of sleep apnea in the elderly, and the high morbidity and mortality of cardiovascular diseases, the search for feasible approaches in primary care that can reduce these outcomes is justified. Thus, the use of HCQ in patients with sleep apnea and at high risk for coronary artery disease represents an entirely new approach to this disease.

### Objectives {7}

#### Main objective

To test in a randomized clinical trial the effect of hydroxychloroquine on endothelial function and its correlates, in elderly people with sleep apnea.

#### Specific objectives

To test in a randomized clinical trial the effect of hydroxychloroquine on endothelial function measured by peripheral arterial tonometry.To test in a randomized clinical trial the effect of hydroxychloroquine on endothelial function measured by flow-mediated dilation of the brachial artery.Compare the endothelial function measured by peripheral arterial tonometry with the endothelial function measured by the mediated flow dilation of the brachial artery in the same individuals to support assessments of the quality of the methodsTest in a randomized clinical trial the effect of hydroxychloroquine on inflammatory markers such as reactive C-protein.Test in a randomized clinical trial the effect of hydroxychloroquine on glycemic homeostasis, assessed by fasting glucose and HbA1c levels.Test in a randomized clinical trial the effect of hydroxychloroquine on the lipid profileTo test in a randomized clinical trial the effect of hydroxychloroquine on the apnea-hypopnea index and the mean and minimum O_2_ saturations assessed by a portable sleep monitoring device

### Trial design {8}

This exploratory study was designed as a randomized researcher and patient blinded controlled trial with a primary endpoint of change in endothelial function after 8 weeks of treatment with hydroxychloroquine. Randomization will be performed as block randomization with a 1:1 allocation ratio.

## Methods: Participants, interventions, and outcomes

### Study setting {9}

The study is conducted in the research laboratory of two academic hospitals in Porto Alegre, Brazil: Hospital de Clínicas de Porto Alegre and Instituto de Cardiologia do Rio Grande do Sul.

### Eligibility criteria {10}

#### Inclusion criteria

People over 65 years oldApnea-hypopnea index greater than 15 events per hour

#### Exclusion criteria

Contraindication to the use of hydroxychloroquine (porphyria, retinopathy, severe hepatic or renal dysfunction, neuropathy and/or muscle disease).Rheumatic diseasesChronic infectionsSerious, terminal, or disabling diseasePrevious ECG with evidence of long QT intervalPrevious or current treatment for obstructive sleep apnea

### Who will take informed consent? {26a}

Members of our research group, formed by nurses, physical educators, nutritionists, medical doctors, and physiotherapists, will obtain informed consent from potential trial participants. After a brief explanation of the study made by phone, we will schedule an appointment for those who are willing to participate. In this appointment, all aspects and details of the study will be explained to the potential participant and the informed written consent will be signed and given a copy to the participant.

## Interventions

### Explanation for the choice of comparators {6b}

Since there is no standard treatment available for endothelial dysfunction, we decided to compare hydroxychloroquine with placebo. The placebo group will receive capsules identical to those of hydroxychloroquine, containing the same excipient as the industrialized product.

### Intervention description {11a}

The intervention group will receive a 400 mg hydroxychloroquine capsule daily for 8 weeks, to be taken with food or milk during lunchtime. Hydroxychloroquine is generally prescribed at a daily dose of 6.5 mg (or less) per kg of body weight (using this formula, the dosage for a 70-kg person would be 455 mg/day). Considering patients newly diagnosed with lupus take 400 mg once daily, we decided to use the same dose due to its known safety and efficacy.

### Criteria for discontinuing or modifying allocated interventions {11b}

The intervention will be discontinued in case of any severe adverse effect or withdrawal of participant consent

### Strategies to improve adherence to interventions {11c}

Every 2 weeks after starting the intervention, participants will receive a call to monitor adherence and adverse effects. At the 8-week follow-up visit, participants will have their unused capsules counted and recorded on the case report form.

### Relevant concomitant care permitted or prohibited during the trial {11d}

The participants are advised to not initiate any new care during the trial. The participant will be excluded from the trial if any new concomitant care needs to be initiated.

### Outcomes {12}

#### Outcomes

##### Main outcome

Difference between the two groups on endothelial function measured by FMD (change of percentage of dilatation of brachial artery diameter from baseline) and PAT (change of reactive hyperemia index of finger from baseline) after 8 week of intervention.

##### Secondary outcomes

Difference between the two groups on changes from baseline in the blood levels of C-reactive proteinDifference between the two groups on changes from baseline in the blood levels of HbA1c fractionDifference between the two groups on changes from baseline in blood levels of fasting glucoseDifference between the two groups on changes from baseline in lipid profile (blood levels of fasting total cholesterol, high-density lipoprotein cholesterol, and triglycerides)Difference between the two groups on changes from baseline in the apnea-hypopnea index and in the mean and minimum oxygen saturation measured with the portable sleep monitoring deviceDifference between the two groups on changes from baseline in weightDifference between the two groups on changes from baseline in systolic blood pressure and diastolic blood pressureComparison between the rate of adverse effects on intervention × control group.

### Participant timeline {13}

Figure 1 shows the time schedule of the study.

**Fig. 1 Fig1:**
[figure not shown]
Time schedule of the study

### Sample size {14}

Based on the effect size estimate of 0.3 standard deviations in the response of endothelial function after HCQ, for a 95% power and 0.05 level of alpha error probability, the sample size was estimated at 20 participants per group. Allowing for extra recruitment to compensate for losses, the sample size will be 25 participants per group, with a sum of 50 individuals.

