## Statistical methods

### Statistical methods for primary and secondary outcomes {20a}

Normally distributed data will be presented as mean and standard deviation. Data not normally distributed will be presented as median and interquartile range. The natural logarithmic transformation of the variable will be used to correct its non-normal distribution in analyses that assume the normal data distribution. The intervention arm (hydroxychloroquine) will be compared against the control for all primary analysis. We will use chi-squared test for binary outcomes, and *T* test for continuous outcomes. We will examine the residual to assess model assumptions and goodness-of-fit. The group × time interaction will be tested using generalized estimating equations. We will use the Bonferroni method to appropriately adjust the overall level of significance for multiple primary outcomes, and secondary outcomes. Results with a probability < 0.05 of alpha error will be considered statistically significant. Statistical analyses will be performed using SPSS software (SPSS Inc., Chicago, IL, USA).

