## Discussion

The COVID pandemics forced changes in protocol. The research center was closed and volunteers were instructed to cancel the visits. This incurred in the loss of 4 subjects. An interim analysis was performed to check for the need to continue recruiting. A new sample size calculation was performed. The large number necessary to obtain 80% power made the project unviable. The investigators decided to abandon the project as initially designed. The finding of a small but significant reduction in the OSA severity may be hypothesis-generating. We may continue searching for possible inflammatory mechanisms and therapeutic targets of OSA.

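### The stated effect (0.3 SD), power (95%), alpha (0.05) and sample size (20 per group) cannot all be true: 0.3 SD with 20 per group gives about 15% power

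*Protocol article*

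**What the plan says.** Under Sample size {14}, the protocol article sets the target as follows: "Based on the effect size estimate of 0.3 standard deviations in the response of endothelial function after HCQ, for a 95% power". Alpha is put at 0.05. From these inputs the section concludes that "the sample size was estimated at 20 participants per group". With an allowance for losses, "the sample size will be 25 participants per group, with a sum of 50 individuals". The section states no sidedness, no correlation between baseline and follow-up, and no effect-size metric other than standard deviations.

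The comparison is fixed elsewhere. Trial design {8} gives 1:1 allocation. Outcomes {12} defines the main outcome as the between-group difference in change from baseline at 8 weeks, for both FMD and PAT. Statistical methods {20a} assigns a t test to continuous outcomes, adds a group-by-time test by generalized estimating equations, and states: "We will use the Bonferroni method to appropriately adjust the overall level of significance for multiple primary outcomes, and secondary outcomes". The sample size section does not mention that adjustment.

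The Discussion reports a new sample size calculation after an interim analysis, with the result that "The large number necessary to obtain 80% power made the project unviable". Trial status says that recruitment will not resume.

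**The concern.** A standardised difference of 0.3 is small, and a parallel-group trial of 40 to 50 people cannot detect it with high power. A claim of 95% power for it is out by a wide margin.

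What is at stake is how the results are read. Someone who relies on the 95% figure would take a non-significant FMD or PAT result as good evidence that an effect of 0.3 SD is absent. If the true power for that effect is about 15%, a non-significant result is the expected finding even when the effect is real.

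**Working it through.** **Inputs.** Effect d = 0.3 SD, power 0.95, alpha 0.05 and n = 20 (25 with losses) come from Sample size {14}. The 1:1 allocation, the between-group comparison of change and the t test come from Trial design {8}, Outcomes {12} and Statistical methods {20a}. A two-sided test is assumed because sidedness is not stated. The value 0.025 per primary outcome is the natural Bonferroni reading for FMD and PAT (0.05 / 2), but the document does not write it out.

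**1. Trying to reproduce 20 per group.** Normal approximation: n per group = 2 (z₀.₉₇₅ + z₀.₉₅)² / d² = 2 × (1.960 + 1.645)² / 0.09 ≈ 289. The exact noncentral t gives 289.7, so 290. The stated 20 is not reproduced; it is short by a factor of about 290 / 20 = 14.5.

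**2. Power at the stated n.** The noncentrality is d√(n/2). For n = 20 it is 0.3 × √10 = 0.949, against a critical t of 2.024 on 38 degrees of freedom. For n = 25 it is 0.3 × √12.5 = 1.061, against 2.011 on 48.

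| Alpha (two-sided) | Power, 20 per group | Power, 25 per group | n per group for 95% | n per group for 80% | Difference detectable with 95% power, 20 per group |
|---|---|---|---|---|---|
| 0.05 | 15.2% | 18.0% | 290 | 176 | 1.17 SD |
| 0.025 | 9.4% | 11.4% | 337 | 213 | 1.27 SD |

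**3. Other readings that keep 0.3 as an SD difference.**
- One-sided test: 242 per group; power at 20 per group is 24%.
- Paired or one-sample t test: 147; power at n = 20 is 25%.
- 0.3 in units of the raw-outcome SD, analysed as change: the effect in change-score units is 0.3 / √(2(1 − ρ)). Power at 20 per group is 12% for ρ = 0.3, 15% for ρ = 0.5, 31% for ρ = 0.8 and 54% for ρ = 0.9. To reach 95%, set 0.3 / √(2(1 − ρ)) = 1.17, which gives ρ ≈ 0.967. The document gives no correlation.
- Adjustment for baseline, same raw-SD reading: 217 per group for ρ = 0.5, 148 for ρ = 0.7, 55 for ρ = 0.9.

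None of these gives 20, short of a correlation near 0.97.

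**4. A reading that does give 20.** Take 0.3 as Cohen's f in a repeated-measures within-between interaction with 2 groups, 2 time points and an assumed correlation of 0.5. The noncentrality is λ = f² × N × 2 / (1 − 0.5) = 0.09 × N × 4 = 0.36N. Power is 94.9% at N = 38 and 95.9% at N = 40, so N = 40, or 20 per group. In the t test on change, λ = d²N/4. Setting d²N/4 = 0.36N gives d² = 1.44 and d = 1.2. That is a difference in change of 1.2 SD, four times the stated 0.3.

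**5. What a null result could show.** With 20 per group, the 95% confidence interval for the difference has half-width 2.024 × √(2/20) ≈ 0.64 SD. An estimate near zero would leave 0.3 SD well inside the interval and 1.2 SD well outside it.

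**The case against.** The arithmetic is not seriously open to dispute; the objections concern what may be built on it, and several of them stand.

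- **Which figure is wrong.** A reader might infer that 20 per group is the error. The document does not support that. On the Cohen's f reading, n and power agree at alpha 0.05 and the label of 0.3 standard deviations is what fails. Neither f nor a correlation of 0.5 appears in the text, so the match is suggestive, not proof. Only the inconsistency is established.
- **The Discussion as a contradiction.** A reader might take the later calculation as an admission that the first was wrong. It gives no effect size, SD, alpha or n, and followed an interim analysis. A smaller observed effect could have demanded a large number even had the original calculation been sound. It is consistent with low power and proves nothing more.
- **Detectable effect and exaggeration.** A reader might call 1.2 SD implausible, or expect any significant estimate to be inflated. The document gives no plausible range for the effect of hydroxychloroquine on either measure. Exaggeration follows only if the true effect is near 0.3 SD.
- **A null result as worthless.** It is uninformative about 0.3 SD, but could argue against effects near 1.2 SD.
- **Warnings already in the article.** The study is called exploratory, and the Discussion says the project was abandoned as designed. This softens the harm, but it does not tell the reader that the original power claim was inconsistent from the start. The exploratory label does not excuse an explicit 95%.

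**Conclusion.** The section is wrong as written. An effect of 0.3 SD, 95% power, alpha 0.05 and 20 per group cannot hold together. Taken at its word on effect and n, the design has about 15% power (18% with all 25 per group), and the n needed for 95% is about 14 times larger. Taken at its word on power and n, the target is a difference of about 1.2 SD. Applying 0.025 per primary outcome lowers the power to about 9% (11%) and moves the detectable difference to about 1.3 SD.

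These figures assume a two-sided test and 0.3 in units of the SD of change. The 0.025 figures also assume that Bonferroni is split equally over FMD and PAT. Reading 0.3 as a raw-outcome SD does not change the conclusion unless the baseline correlation is about 0.967. The number finally evaluable is not stated; fewer than 20 per group would give less power still. Confidence in the inconsistency is high; its origin remains open.

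**What to change.** Restate Sample size {14} so that effect, metric, alpha, power and n agree:

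- Name the effect-size metric actually used. If it was Cohen's f = 0.3 in a repeated-measures interaction, say so, with the assumed correlation and the equivalent difference in change of about 1.2 SD.
- Give the power delivered at the alpha that matches the Bonferroni rule in Statistical methods {20a}. Suggested wording, if the adjusted level is 0.025: *With 20 evaluable participants per group and a two-sided test at 0.025 for each primary outcome, power for a 0.3 SD difference in change is about 9% (15% at 0.05). Power of 95% is reached for a difference of about 1.3 SD (1.2 SD at 0.05).* Replace 20 by the evaluable number if it differs.
- Report FMD and PAT as between-group estimates with confidence intervals, and do not read a non-significant result as excluding an effect of 0.3 SD.

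The cost is wording and a less favourable stated power. With recruitment closed, the remedy is correction and cautious interpretation; no extra patients are needed.
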